**A.4 METHODOLOGY**

Outline how you intend to achieve the objectives of the study.

*Guidance notes:*

*For each objective/hypothesis:-*

- *define the target population*
- *describe how the sample(s) is(are) to be recruited from the target population(s)*

*Even if the main thrust of the research is biomedical, the rationale behind your use of social science methods (e.g. patient interviews) should be clear.*

We intend to achieve the objectives of our study through two different research aspects, one focusing on non-clustered randomization (sample size of 288) and other looking specifically at randomized clusters (sample size of 550). We have clustered at the community level to observe for an effect of fOBU on increasing overall ANC attendance. We have randomized at the patient level for assessment of the efficacy of medical/dental outreach with fOBU to change patient preference for delivering in a health care center.

Communities in the Kabale District will be assessed for population size, demographics and birth rate. Communities that have similar characteristics will be selected and contacted to engage in the study. Communities who agree to participate in this study will be contacted and community leaders will make announcements at local schools, churches, and community events regarding the upcoming free antenatal clinics. During these announcements the community will be told either a) that there will be structured maternal health camps (sMHC) offering free obstetric ultrasound (OBU) or b) that there will be sMHCs with no mention of the fOBU. In actuality, to assure that all women are given the benefit of optimal care, all SMHCs will provide fOBU, but only the advertising messages will differ between groups. Communities will be stratified by catchment population (small, medium or large) prior to randomization and assignment to the intervention or control group. Additionally, we will be collecting demographic data on registration to clinic and asking a pre clinic questionnaire to assess maternal feelings towards the healthcare system, and their preferences for where to deliver their baby (at a healthcare center or at home).

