Sample size calculations were considered for two of the primary outcomes. For the first outcome – looking to determine the efficacy of portable ultrasound in improving maternal uptake of antenatal care due to portable ultrasound being offered – a simple randomization based on communities will be utilized. For the additional outcome of eliciting a change in patient preference for delivering at a healthcare facility before and after a rural outreach clinic the communities will be both clustered and randomized. In this case a design effect is added to account for the clustering for this patient-level outcome.

1. Facility based uptake of ANC (no clustering): At a two-sided alpha of 0.05 and holding power at 80%, with p1 of .70 and p2 of 0.52 [1], then 144 pregnant women will be required in each of the control and intervention groups. Inflating this by 25% to prepare for any non-consent and/or non-response, the required sample increases to 180 women per group. From experience gained in our pilot study, we anticipate that health facilities will enroll a greater number of women, therefore our sample will provide more than adequate power. We will conduct power calculations during analysis, however, we anticipate power of greater than 90%.
2. Patient-level outcomes (clustered): At a two-sided alpha of 0.05 and holding power at 80%, using an estimated intracluster coefficient (ICC) of 0.1 [2], with p1 of 0.95 and p2 of 0.85, and an average cluster size of 60 pregnant women (m), then 225 pregnant women will be required per study arm, which is equivalent to needing 4 clusters per group. Inflating this by 25% to account for potential non-response gives 282 pregnant women per group.

Notes:

1. Rate of uptake of antenatal care (at least 1 ANC visit) in pilot studies in our community
2. Generally, ICCs are not known prior to study start. For ICC assumption, it is generally accepted that clinical outcomes have ICCs of around .05; whereas process outcomes (which our research is studying) range from 0.05 to 0.15; we have used 0.1 in our calculations.

Reference: <http://www.who.int/reproductivehealth/topics/best_practices/intracluster_correlation.pdf>

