Although this comprehensive approach would offer many potential benefits to both mother and infant, local thought leaders believe that women do not see these interventions as significant, and therefore do not present for care even when mobile free clinics are brought into their communities. The impression of the local medical staff is that the importance of these “low tech” interventions are not appreciated in the general community. On the other hand these same thought leaders have suggested that women would present for care to have the concrete outcome of “seeing a picture of the baby”. In addition to being appealing to women who are pregnant for personal reasons, studies have shown that obstetric ultrasound imaging can prevent many serious complications of pregnancy (listed previously) by providing early diagnosis and intervention. For example, by providing useful information such as whether or not the mother is carrying twins, has an ectopic pregnancy or placenta previa, a mother and her partner can make an informed decision about whether or not to deliver at home with untrained professionals, or a health center where they can receive life-saving treatment.^1^ Furthermore, the World Health Organization (2003) recognizes ultrasound technology as ideally suited to low and middle income countries, as it is relatively low-cost, low input, and easily maintained and transported. Additionally, studies conducted on the use of ultrasound technology in two rural hospitals in Rwanda have indicated that after an initial training period, an ultrasound program led by local health care providers can be sustainable and lead to accurate diagnoses.^2^ Ultrasound imaging is beneficial to rural populations as it is a simple a non-invasive procedure. This helps to reduce levels of fear from women who have previously maintained their cultural preferences for receiving treatment and giving birth with untrained birth attendants in their local villages.^3^

We carried out a small pilot program in March 2013 that screened 48 antenatal women with free mobile ultrasound. We found the technology to work well within the local context and women routinely expressed their appreciation and impression that they were glad they had come and would recommend it to their peers. All of the above routine antenatal screening and interventions were offered at the same time as per routine local guidelines.

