**3. Design and Methodology**

Communities in the Kabale District will be assessed for population size, demographics and birth rate. Communities that have similar characteristics will be selected and contacted to engage in the study. Communities who agree to participate in this study will be contacted and community leaders will make announcements at local schools, churches, and community events regarding the upcoming free antenatal clinics. During these announcements the community will be told either a) that there will be structured maternal health camps [sMHC] offering free obstetric ultrasound [fOBU] or b) that there will be sMHCs with no mention of the fOBU. In actuality, to assure that all women are given the benefit of optimal care, all SMHCs will provide fOBU, but only the advertising messages will differ between groups. Communities will be stratified by catchment population (small, medium or large) prior to randomization and assignment to the intervention or control group. The sMHCs will be organized in collaboration with TO – the WORLD and KIHEFO. The four-pronged approach of MTCT elimination will be followed in the design of the sMHC. This will include primary prevention of HIV, prevention of unintended pregnancies, prevention of vertical transmission and assuring linkages to care treatment and follow-up. Each sMHC will take place over a 12-hour period. All women who appear for clinic will be registered, with demographics recorded, and go through a triage process. They will then receive pre-test counseling for HIV, followed by blood sample collection for onsite testing for HIV/syphilis/hepatitis B, they will then go through family planning sessions, receive a fOBU, will be seen by a triage nurse and then be seen by an MD or DDS (Dentist) depending on their triage needs. All routine care including iron, folate and intermittent presumptive therapy for malaria will be offered free of charge. Women who are found on ultrasound screening to have potential obstetrical high risk pregnancies (low lying placenta, twins, potential birth defects) will be referred for local obstetrical services in Kabale (the regional referral center). Ultrasound will be performed using two Sonosite 180 portable ultrasonographic units operated by two technicians trained to levels of competency as dictated by national guidelines.

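### Item 1 of A.5.4 is powered on having at least one ANC visit, but the trial observes attendance at its own health camps, so the 80% and over-90% power statements do not describe the uptake endpoint

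*Protocol*

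**What the plan says.** Protocol A.5.4, item 1, sets the planning values: "At a two-sided alpha of 0.05 and holding power at 80%, with p1 of .70 and p2 of 0.52 [1"]. It concludes "then 144 pregnant women will be required in each of the control and intervention groups", and then "Inflating this by 25% to prepare for any non-consent and/or non-response, the required sample increases to 180 women per group". It expects larger enrolment and adds "we anticipate power of greater than 90" per cent. The note marker follows 0.52, and the note reads "Rate of uptake of antenatal care (at least 1 ANC visit) in pilot studies in our community". No source is given for 0.70.

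Elsewhere the protocol describes what will be observed:
- A.8 gives the primary objective as the number of women presenting at the clinics with and without the intervention, captured at triage.
- Section 3 (Design and Methodology): "Each sMHC will take place over a 12-hour period". The number of camps per community is not stated.
- Section 5 enrols pregnant adults who present at a camp.
- A.6.1 lists a maternal survey and an exit survey, and nothing for women who do not attend.
- A.7 compares uptake between arms by linear regression at health-centre level.
- A.4 says communities were clustered "to observe for an effect of fOBU on increasing overall ANC attendance".

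**The concern.** Having had at least one antenatal visit and attending a particular camp are different proportions. A woman who had routine care elsewhere but missed the camp counts towards the first and is invisible to the trial. Every enrolled woman is an attender, so the proportion used for sizing cannot be estimated from enrolled women.

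The protocol's own Background also discourages carrying the rate across. It reports that women "do not present for care even when mobile free clinics are brought into their communities". The one pilot it describes gives 48 women screened, with no denominator and no rate.

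At stake are the power statements for the stated primary objective and the breadth of the claim in A.4.

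**Working it through.** **1. The two proportions side by side.** The planning rate is at least one ANC visit. A.2 gives about 60% for Kabale on that measure. The Background gives 66%, set against about 95% in urban areas attending at least once before delivery. The observed quantity is presentation at a 12-hour camp. A camp visit is one way to reach at least one visit, but not the only way, so the two rates need not agree.

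**2. The plan's own figure.** Inputs from A.5.4: two-sided alpha 0.05, power 80%, p1 = 0.70, p2 = 0.52, no clustering. With mean p̄ = 0.61, the pooled two-proportion formula is

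n = [1.96·√(2p̄(1−p̄)) + 0.8416·√(p1(1−p1) + p2(1−p2))]² / (p1−p2)²

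= (1.96 × 0.6898 + 0.8416 × 0.6779)² / 0.0324 = 3.696 / 0.0324 = 114.1, so 115 per arm (125 with continuity correction).

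The stated 144 is not reproduced. It equals 115 × 1.25 = 143.75 rounded up, so the 25% inflation may have been applied twice to reach 180. That is a separate matter.

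Power = Φ{[|p1−p2|·√n − 1.96·√(2p̄(1−p̄))] / √(p1(1−p1) + p2(1−p2))}. At n = 144 this is Φ[(2.160 − 1.352) / 0.678] = 88%. At n = 180 it is 94%. The over-90% figure is therefore reachable, but only for 0.70 against 0.52 and without clustering.

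**3. The same formula for camp attendance.** The documents give no camp-attendance rate, so the control rates below are assumptions. Three ways of carrying over the planned effect are shown: ratio 0.70/0.52 = 1.35, odds ratio (0.70/0.30)/(0.52/0.48) = 2.15, and difference 0.18. Power is at 144 per arm without clustering, with the intervention rate in brackets.

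| Control | Same ratio | Same odds ratio | Same difference |
|---|---|---|---|
| 0.10 | 15% (0.135) | 61% (0.193) | 98% (0.28) |
| 0.20 | 28% (0.269) | 82% (0.350) | 92% (0.38) |
| 0.30 | 45% (0.404) | 88% (0.480) | 88% (0.48) |
| 0.40 | 65% (0.538) | 90% (0.589) | 87% (0.58) |

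**4. Changing the denominator.** Step 3 treats 144 as all the pregnant women in an arm. Item 2 of A.5.4 plans an average of 60 women per cluster and 4 clusters per group. If those 60 are camp attenders, lower attendance means a larger catchment. Keeping the ratio of 1.35, still without clustering:
- Control 0.10: 60/0.10 = 600 per community, × 4 = 2,400 per arm, power 96%.
- Control 0.20: 300 per community, 1,200 per arm, power 98%.
- Control 0.30: 200 per community, 800 per arm, power 99%.

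Dividing 60 by the mean attendance of the two arms instead gives 93%, 96% and 98%.

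**5. Why step 4 is not a usable restatement either.** Communities are randomised (section 7), so step 4 overstates the information. As an illustration only, take the ICC of 0.1 that item 2 assumes for a different outcome. At 200 women per community the design effect is 1 + 199 × 0.1 = 20.9, and 800 women per arm carry the information of about 800/20.9 = 38.

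**The case against.** The strongest reply is that 0.52 may already be a camp-type rate. The note does not say whole pregnancy. The phrase about attendance before delivery belongs to an urban coverage statistic, not to the pilot. The one pilot described was a free mobile ultrasound programme, much like the camps, and A.8 itself calls the camps ANCs. That 0.52 differs from 60% and 66% is at least compatible with a different measure. This stands as a caution: cumulative coverage over pregnancy is the ordinary reading of the note, not its wording. It does not rescue the plan, because the pilot reports no denominator and nothing in the protocol shows 0.52 to be camp attendance.

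A second reply is that the population and birth-rate data in A.4 could supply a denominator. They could, but the protocol does not use them so, and the result would be a camp-attendance proportion, still not the one used for sizing.

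A reader might infer from the first column of the table that the trial is badly underpowered. The documents do not support that. That column holds 144 fixed as every pregnant woman in the arm and uses the least favourable effect scale. High power is not confined to an unchanged 18-point difference either: the same odds ratio gives 90% at a control rate of 0.40. A reader might also infer a single camp per community, or that the cluster size of 60 was derived from 0.52. Neither is stated.

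**Conclusion.** The point holds as a mismatch between the planning rate and the observed endpoint. The 80% and over-90% statements are attached to a proportion that the trial's data cannot estimate, and overall ANC attendance in A.4 is wider than camp counts can show.

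How far the power is wrong, and in which direction, is not established. The 15% to 98% range rests on assumed control attendance of 0.10 to 0.40, three effect scales, 144 women per arm and no clustering. The catchment figures rest on one camp of 60 attenders in each of 4 communities per arm. The conclusion rests on reading the note as coverage from any provider, which A.2 and the Background support but the note does not spell out.

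Because the protocol itself fixes these inputs and power claims, the correction belongs in the protocol.

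**What to change.** In A.5.4, item 1:
- Remove the 80% and over-90% power statements tied to 0.52 and 0.70.
- Define uptake as camp attenders divided by expected current pregnancies in the community, using the population and birth-rate data that A.4 already assesses.
- State an assumed control attendance and a target effect for that measure. Take them from pilot or outreach records if these have a denominator. Otherwise give an explicit range.
- Restate power at the planned number of communities, allowing for community randomisation, with expected pregnancies per community as the denominator in place of 144 women.

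In A.4, limit the claim to attendance at the free maternal health camps.

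The cost is one recalculation and a text amendment, with no new procedures. The stated power becomes a range and may be less favourable. If it proves low, the sponsor must decide whether to add communities or accept the limitation.

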**A.6 PROCEDURES**

A.6.1What procedures or methods will be employed in the collection of data (e.g. patient interviews / focus group discussions / blood sampling / biopsies) and by whom (e.g. experienced facilitator / social scientist / teacher/ qualified doctor / nurse, auxiliary, etc.)?

Attach additional sheets if necessary.

| **Procedure** | **To be carried out by:** |
| --- | --- |
| **Maternal survey** | **Qualified research associate** |
| **Exit Survey** | **Qualified research associate** |
|  |  |
|  |  |
|  |  |
|  |  |
|  |  |

A.6.2 State the extent to which the procedures to be used are a part of usual clinical management (if appropriate).

In this case the intervention – a free obstetric ultrasound – has low risk for potential adverse outcomes. False positive screening ultrasound identifying non-existent congenital anomalies may lead to maternal concern. Any women who have an examination that demonstrates concerning findings will be transferred free of charge to a tertiary care facility for obstetrical consultation and confirmatory testing. Thus, the benefit of early identification and management of true positive tests with prevention of maternal and fetal adverse outcomes will outweigh the potential risk of rare false positive testing.

A.6.3 Please indicate that the persons identified in A.6.1 are competent to carry out these procedures. List any training of staff that may be required prior to commencement of the study.

[name]: Bachelor of Sciences, major in Biology, with a minor in neurosciences

[name]: Bachelor of Sciences, major in Biology

No training will be required prior to the commencement of the study

**A.7 ANALYSIS**

A.7.1 What are the major statistical (or other) methods that you intend to use to analyse the data to

fulfill each of the objectives/hypothesis stated in A.3

As it is recommended in cRCT, and in particular with relatively few numbers of clusters, to assess the effectiveness of randomization we will first examine the baseline characteristics of the health centre clusters and the individual patients across intervention and control groups. Analyses will be done at both health facility and individual (patient) levels, adjusted for clustering. Health center level analyses will use multivariable linear regression to compare uptake between the intervention and control arms, adjusting for potential confounders. At the patient level, to adjust for cluster randomization, we will use generalized estimating equation binomial regression models with log link and exchangeable correlation structures to estimate the relative risks (RR) and 95% confidence intervals for rates of patient preference for delivery site between the intervention group (receive fOBU messaging) with the control group as a reference. STATA version 9.2 (Stata Corp, College Station, TX) or equivalent will be used for all analyses.

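### Characteristics of attenders cannot test the randomisation or adjust uptake, and an uncapped confounder adjustment does not suit about 8 to 10 cluster-level observations

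*Protocol*

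**What the plan says.** Protocol A.7 begins with a check on the allocation: "to assess the effectiveness of randomization we will first examine the baseline characteristics of the health centre clusters and the individual patients". It gives the small number of clusters as a reason for doing so. For the uptake outcome it then says: "Health center level analyses will use multivariable linear regression to compare uptake between the intervention and control arms, adjusting for potential confounders". No confounder is named and no limit is set on their number.

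On where individual data come from:
- A.4 places the demographic data and the questionnaire at the clinic, on registration.
- A.5.3 and section 5 include only pregnant women who present to a camp.
- A.6.1 lists two data-collection procedures, a maternal survey and an exit survey.
- The announcements that differ by arm come before all of this (A.4 and section 3).

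On the design, section 3 says: "Communities will be stratified by catchment population (small, medium or large) prior to randomization", and A.4 says the same. A.5.4 calls the randomisation for the uptake outcome simple. A.7 does not mention the strata.

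The only cluster count is in item 2 of A.5.4, for the patient-level outcome: "then 225 pregnant women will be required per study arm", "which is equivalent to needing 4 clusters per group", inflated to 282 women per group. Item 1, on uptake, gives no number of communities.

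**The concern.** A baseline check asks whether chance produced comparable groups. It works only on data that the intervention could not have affected. Here the randomised message acts on attendance, and only attenders are measured. If the message works as A.3 expects, it brings in women who would otherwise have stayed away, so attenders may differ between arms even when the randomisation was perfect. The check as written could report an intervention effect as failed randomisation. If the same variables were used to adjust uptake, the model would condition on something the intervention may have changed.

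Separately, a linear regression on community-level uptake has one observation per community. With very few communities, every covariate takes a noticeable share of the information available to estimate error. An unlimited confounder set can leave the main objective (A.8.1) without a usable confidence interval. A.7 does not name catchment size, the one covariate that the design itself justifies.

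**Working it through.** **Step 1. Order of events.** Communities are randomised; announcements differ by arm; women decide whether to come; those who come are registered and questioned. Individual characteristics are therefore observed only after, and conditional on, the uptake outcome. A fixed trait such as age is not altered by the message, but the mix of women observed can be.

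**Step 2. How large a shift could be.** Inputs: the uptake rates in A.5.4, 0.70 and 0.52. Assume that the ultrasound message deters nobody. The share of intervention-arm attenders who would not have come under the control message is then (0.70 − 0.52)/0.70 = 0.18/0.70 = 0.257. If a trait's prevalence differs by d between these extra women and the rest, the arms differ by 0.257 × d with perfect randomisation. The documents give no d. For assumed values of 10, 20 and 40 percentage points, the shift is 2.6, 5.1 and 10.3 points.

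**Step 3. Number of communities.** At the stated average of 60 women per cluster, 225/60 = 3.75, so 4 per arm and 8 in total, as the protocol says. After inflation, 282/60 = 4.7, so 5 per arm and 10 in total. The total of 550 in A.4 gives 550/60 = 9.2. A range of 8 to 10 is fair for the trial as planned.

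The 225 does not itself follow from its stated inputs ("with p1 of 0.95 and p2 of 0.85"; "using an estimated intracluster coefficient (ICC) of 0.1"). Without clustering, those rates need 141 women per arm. The design effect is 1 + (60 − 1) × 0.1 = 6.9, and 141 × 6.9 = 973, or 17 clusters per arm. That is a separate problem. It matters here only because a larger trial would ease the shortage of degrees of freedom.

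**Step 4. Residual degrees of freedom.** Residual df = communities − 2 − q, where q is the number of covariate terms beyond arm. A three-level stratum uses q = 2.

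**Step 5. Effect on precision.** Assumptions, none of them stated for uptake: ICC 0.1, 60 women per community as the uptake denominator, rates 0.70 and 0.52, and covariates that explain no variation. The variance of a community proportion is p(1 − p)[ICC + (1 − ICC)/m]. The bracket is 0.1 + 0.9/60 = 0.115, so the variances are 0.21 × 0.115 = 0.02415 and 0.2496 × 0.115 = 0.02870. The SE of the difference is √(0.05285/4) = 0.115 with 4 communities per arm, and √(0.05285/5) = 0.103 with 5. The half-width is t × SE; power is from the noncentral t distribution.

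| q | 8 communities: df, t | Half-width | Power | 10 communities: df, t | Half-width | Power |
|---|---|---|---|---|---|---|
| 0 | 6, 2.447 | 0.28 | 0.262 | 8, 2.306 | 0.24 | 0.339 |
| 2 | 4, 2.776 | 0.32 | 0.228 | 6, 2.447 | 0.25 | 0.315 |
| 3 | 3, 3.182 | 0.37 | 0.199 | 5, 2.571 | 0.26 | 0.297 |
| 4 | 2, 4.303 | 0.49 | 0.157 | 4, 2.776 | 0.29 | 0.272 |
| 5 | 1, 12.706 | 1.46 | 0.101 | 3, 3.182 | 0.33 | 0.235 |

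With 8 communities, q = 6 saturates the model and leaves no interval. Over the ICC range of 0.05 to 0.15 given in A.5.4, power with 8 communities goes from 0.413 to 0.198 at q = 0, and from 0.229 to 0.126 at q = 4. The difference sought is 0.18.

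**The case against.** The strongest reply is that A.7 never connects its two parts. A reader might infer that confounders will be picked after looking at observed imbalance, or taken from the attender data. The text says neither. The uptake model is at health-centre level, and A.4 names community variables assessed before randomisation (population size, demographics, birth rate) that would be legitimate covariates. This stands: distortion of the uptake estimate by attender mix is a risk that the wording leaves open, not something that the protocol commits to. Comparing cluster-level baseline data is also sound.

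A covariate list is ordinary content for a statistical analysis plan, which may exist. That stands for the list itself. It does not cover the attender check, which A.7 states outright.

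A reader might take the missing stratum as a source of bias. The documents do not support that. Catchment population could be among the intended confounders, and leaving a design stratum out of a linear model mainly affects precision and the standard error. Nor does it follow that the patient-level model needs the stratum: with few clusters and expected rates of 0.85 to 0.95, an extra term in a log-link binomial GEE may cause convergence problems.

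Finally, the table assumes covariates that explain nothing. A strongly prognostic one would reduce residual variance and could repay its degree of freedom, particularly if uptake were analysed as a count, where catchment size could matter a great deal. That is a reason to include the stratum, but not to leave the set open.

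**Conclusion.** The concern holds in a limited form. The firm part is that A.7 uses individual characteristics of attenders to assess the randomisation, and data collected after and through the randomised message cannot do that. With the protocol's own uptake rates, and if nobody is deterred, about 26% of intervention-arm attenders would be women drawn in by the message. An arm difference among attenders is therefore to be expected whenever those women differ from the rest. Such variables are unsafe for adjusting uptake.

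The second part is one of proportion. On 8 to 10 communities, arm alone leaves 6 to 8 residual df. Going from no covariate terms to four widens the half-width from about 0.28 to 0.49 with 8 communities, and from about 0.24 to 0.29 with 10. These figures rest on the assumptions in the working. The count is borrowed from the patient-level calculation, so treating exactly 8 as the planned number for uptake would go beyond the text. The missing stratum is the weakest part and is a matter of precision and standard errors only.

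**What to change.** First reconcile the simple randomisation described in A.5.4 with the stratification in A.4 and section 3, since the model should follow whichever was used. If stratification is confirmed, reword A.7 as follows:
- Assess balance only on community data fixed before randomisation: population size, demographics and birth rate.
- Report characteristics of attenders by arm descriptively, as a possible result of the messaging, and exclude them from the uptake model.
- Fix the primary uptake model as arm plus catchment-size stratum, with inference from t on the residual df.
- Put any further pre-randomisation community covariate in a sensitivity analysis only.

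No new data are needed. The cost is the loss of flexible covariate choice and 1 to 2 df for the stratum. As a three-level factor it leaves 4 df with 8 communities and 6 with 10. As an ordered score it leaves 5 and 7, but assumes a linear trend across the three sizes. The rewording does not make a trial of this size well powered; it only avoids spending further the little information there is.

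### Delivery preference is to be analysed by GEE with about 4 communities per arm and no small-sample method; with the usual large-sample inference the 5% test rejects a true null about 10-13% of the time

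*Protocol*

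**What the plan says.** Section 7 (Statistical Design) randomises communities to two messaging arms. A.5.4 item 2 sizes the delivery-preference outcome: "At a two-sided alpha of 0.05 and holding power at 80%, using an estimated intracluster coefficient (ICC) of 0.1", rates of 0.95 and 0.85, and 60 women per cluster on average. It concludes "then 225 pregnant women will be required per study arm, which is equivalent to needing 4 clusters per group". It adds: "Inflating this by 25% to account for potential non-response gives 282 pregnant women per group". The note on the ICC says that process outcomes "range from 0.05 to 0.15; we have used 0.1 in our calculations".

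A.7.1 sets the patient-level analysis: "generalized estimating equation binomial regression models with log link and exchangeable correlation structures", giving a relative risk and 95% confidence interval for intervention against control. The same paragraph recognises the difficulty, "in particular with relatively few numbers of clusters", but what follows from it is an examination of baseline characteristics. It does not state robust or model-based standard errors, a normal or t reference, a bias-corrected variance, a permutation test, or a cluster-level comparison for this outcome.

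**The concern.** GEE inference is justified by a large number of clusters, not a large number of women. With 4 clusters per arm two things go wrong together. The ordinary robust (sandwich) variance is too small, because it in effect divides by k clusters per arm where k-1 is needed. The normal critical value of 1.96 also replaces a t value on about 6 degrees of freedom. Checking baseline balance addresses neither.

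A.5.4 counts delivery preference among the primary outcomes that it sizes, and section 2 lists it as an objective. At stake is a false claim that advertising ultrasound changes where women want to deliver, supported by an interval narrower than the data warrant.

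**Working it through.** **Inputs.** From A.5.4 item 2: two-sided alpha 0.05, power 80%, rates 0.95 and 0.85, m = 60, ICC 0.1 (own range 0.05-0.15), 225 women per arm, 282 after inflation. From A.7.1: the GEE model. Assumed, because not stated: robust standard error, normal reference, no covariates, equal clusters, beta-binomial data.

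**Step 1: the plan's cluster count.**
- 225/60 = 3.75, so 4 per arm. After inflation, 282/60 = 4.7, so at most 5.
- The 225 does not follow from the stated ICC. Without clustering, n = [1.96·√(2·0.90·0.10) + 0.8416·√(0.95·0.05 + 0.85·0.15)]² / 0.10² = 140.1, so 141 per arm.
- The design effect is 1 + 59·0.1 = 6.9, and 141·6.9 = 973 per arm. 973/60 = 16.2, so 17 clusters per arm.
- 225 is matched only with ICC 0.01: 141·1.59 = 224.

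That discrepancy is a separate point, but it is why so few clusters are planned.

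**Step 2: analytic type I error.** With k equal clusters per arm and only the arm term, the sandwich SE is √((k-1)/k) times the cluster-level t-test SE. The rejection rate under the null is therefore P(|t on 2k-2 df| > 1.96·√((k-1)/k)).
- k = 4: SE ratio √(3/4) = 0.87. P(|t6| > 1.697) = 14.1%.
- k = 4 with an overall K/(K-1) = 8/7 variance factor: P(|t6| > 1.815) = 12.0%.
- k = 17: P(|t32| > 1.901) = 6.6%.

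**Step 3: simulation under the null.** Beta-binomial data, common rate 0.85 to 0.95, 60 women per community.

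| Setting | Type I error |
|---|---|
| 4 per arm, plain sandwich, z, ICC 0.05-0.10 | 10.5-13.2% |
| Same, at the planned ICC 0.1 (rates 0.85 / 0.90 / 0.95) | 12.1 / 11.8 / 10.6% |
| 4 per arm, K/(K-1) factor, z, ICC 0.05-0.10 | 8.4-11.0% |
| 4 per arm, plain sandwich, z, ICC 0.15 | 8.7-11.2% |
| 4 per arm, model-based exchangeable SE, ICC 0.1 | 13.4-14.6% |
| 5 per arm, plain sandwich, z, ICC 0.05-0.10 | about 9-11% |
| 4 per arm, k-1 divisor and t on 6 df, ICC 0.05-0.10 | 2.5-4.5% |
| 4 per arm, t test on community proportions, ICC 0.1 (rates 0.85 / 0.90 / 0.95) | 4.5 / 4.1 / 3.1% |

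Full GEE fits at ICC 0.1, with fewer replicates, agree: 10.6-13.1% with equal clusters and 11.6-13.7% with unequal ones. Combining the milder choices (5 per arm, K/(K-1) factor, ICC 0.15) brings the rate down to about 6%.

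**Step 4: interval width at 4 per arm, relative to plain sandwich with z.** In this balanced layout the Kauermann-Carroll correction equals the k-1 divisor.
- Kauermann-Carroll with t on 6 df: (2.447/1.96)·√(4/3) = 1.44.
- Mancl-DeRouen with t on 6 df: (2.447/1.96)·(4/3) = 1.66.

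**The case against.** The strongest reply is that A.7.1 names an estimator and not a variance or a critical value. Those details commonly go into an SAP, and a corrected GEE is compatible with every word of A.7.1. This stands in part. A reader might infer that the protocol prescribes an uncorrected analysis; it does not, and the sizes above hold only if conventional inference is used. The point still holds because A.7.1 chooses the model, link, correlation structure and interval for a design with about 8 clusters, recognises that they are few, and draws only a baseline check from that. Model-based standard errors would not rescue it.

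A reader might also infer that a false positive is at least twice as likely as stated. That is too strong. It holds for the plain sandwich with 4 per arm at ICC 0.05-0.10, but some rates fall below 10% with a K/(K-1) factor, with 5 per arm, or at ICC 0.15, the top of the protocol's own range.

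Two further limits stand. The problem is partly a consequence of the cluster count: with 17 per arm the analytic rate is 6.6%. And it does not touch ANC attendance, which A.8.1 calls the primary objective and A.7.1 analyses by health-centre-level linear regression.

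**Conclusion.** The point holds in a conditional form. The method named for delivery preference does not suit the number of communities planned unless a small-sample method is added, and none is named. With robust standard errors and a normal reference, type I error is about 10-13% at 4 communities of 60 per arm and ICC 0.05-0.10. It is roughly 6-15% over the choices that the protocol leaves open: finite-sample factor, model-based standard errors, 5 communities per arm, ICC up to 0.15. Every uncorrected variant examined exceeds 5%, and the confidence intervals are too narrow to match. The figures rest on beta-binomial data, no covariates and mostly equal cluster sizes. This should be corrected, but it is a matter of analysis wording and not a flaw in the randomisation or data collection.

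**What to change.** State in A.7.1 that delivery preference will be analysed in one of two ways, chosen before the data are seen, with confidence intervals on the same basis:

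- a t test on community-level proportions, with degrees of freedom equal to the number of communities minus 2; or
- the same GEE with a Kauermann-Carroll corrected variance and a t reference, with degrees of freedom equal to the number of communities minus the number of cluster-level parameters. This option keeps the relative risk directly.

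Mancl-DeRouen should not be paired with the t reference here: at 4 per arm the intervals would be about 66% wider, and the simulated type I error is only about 1.4-2.7%.

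The cost is a sentence of text and honest precision. At 4 communities per arm, the k-1 divisor with t on 6 df gives intervals about 44% wider than the plain sandwich with z, and a somewhat conservative test (about 2.5-4.5%). If the number of communities is raised when the A.5.4 calculation is reconciled with its stated ICC, both the problem and this cost become small.
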